#### Aim 2: Health Outcomes

Health outcomes will be measured upon joining the study at baseline (week 0), posttransplant (~week 3), before discharge (~week 6), midintervention or wait period (~week 10), and at the end of the 8-week home intervention or wait period (~week 14). WC participants will undergo additional health measurements at week 18 (midintervention) and after week 22 (postintervention). Health outcomes will include self-reported global health and lung function.

Self-reported global health will be measured by the National Institutes of Health (NIH) Patient-Reported Outcomes Measurement Information System (PROMIS) Pediatric Global Health Scale Short Form 7+2 (PGH-7+2) survey [58,59]. The original PGH-7 has been tested for validity among representative samples in a variety of pediatric clinical groups [59-61]. The PGH-7+2 includes 7 questions from the original scale that ask about general health, general quality of life, general physical health, general mental health, the frequency of feeling sad, the frequency of having fun with friends, and the frequency of caregivers listening to ideas, along with 2 additional questions: the frequency of feeling and trouble sleeping. Lower scores indicate a poorer response. The PGH-7+2 is scored by summing the values of the first 7 questions that correspond to global health, which will be transformed into a raw T-score and an SE using tables provided by survey developers. The last 2 questions are not scored as part of global health; instead, they are reported as raw response scores. A T-score of 50 is the average for the US population, with an SD of 10. Research staff will have 2 versions of the PGH-7+2 available to account for differing abilities and preferences: a caregiver proxy report version and a pediatric self-report version. Lung function will be measured by a test of forced expiratory volume using a peak flow meter. The participants will be instructed to forcefully exhale as hard as they can into the peak flow meter. The test will consist of 3 trials, where the average will represent the final value for lung function.

#### Aim 3: Intervention Acceptability

Intervention acceptability will be measured through participant engagement. Participant engagement outcomes will include enrollment, dropout, adverse events, and attendance rates. Attendance to the ER prescription will be expressed as a percentage of the minutes of gaming performed, divided by the minutes prescribed. Minutes of exercise will be recorded automatically by the headset in the built-in Meta Quest Move app. Meta Quest Move tracks active minutes of play each day, which can be archived for a year and be accessed either in the headset or through the Meta mobile phone app. The Move app also allows users to set weekly goals that include built-in notification features on goal progress. Research staff will set up Move goals to match the dose of intervention prescribed in the hospital and instruct caregivers to modify the goals when participants exercise at home.

### Statistical Analysis

Descriptive statistics, including means, SDs, and CIs, will be obtained for all study variables, and longitudinal smoothed scatterplots will be examined to identify temporal trends between groups, including the presence of potentially important nonlinear time trends. For aim 1 and aim 2 (measures of outcomes), outcomes will be modeled using all available measures, using mixed models with each participant included as a random effect to account for the repeated measures. Changes in means will be estimated with confidence intervals and compared between groups at 5 time points, which are baseline (week 0), posttransplant, hospital discharge (~week 6), midintervention or wait period (week 10), and postintervention (week 14) using estimated marginal means (also called least squares means). For aim 3, estimates with 95% CIs will be obtained for enrollment, dropout, and adverse event rates. Statistical tests will be 2-sided and will be performed using a significance level of *P*<.05. Statistical analyses will be performed using R (R Development Core Team) version 4.3.1 or higher (R Foundation for Statistical Computing).

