### Measures

All measures for this study will attempt to be conducted remotely, when possible. There are a total of 5 data collection time points that will be compared between groups, which are baseline (week 0), posttransplant (~week 3), hospital discharge (~week 6), the middle of the home intervention or wait (week 10), and postintervention (after week 14). WC participants will undergo 2 additional measurements, a mid- (week 18) and postintervention measure (week 22) of their home intervention. The first data collection visit will occur in person, and participants will be guided through the measurement instruments. The remaining 4 data collections will be conducted through phone or videoconference. The rationale for doing so is to simulate a remotely conducted trial and thus allow for easier replication in a future multisite trial. In addition, research staff would not have to track down participants in various clinics throughout their treatment and outpatient rehabilitation phases.

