#### Aim 1 (Primary Outcome): Physical Activity

Physical activity level will be measured by steps per day using a Fitbit Flex 2 wrist-worn tri-axial accelerometer. The participants from both the IS and WC groups will be equipped with the Fitbit Flex as soon as they join the study. IS participants will wear the Fitbit Flex and daily steps will be measured until they complete the entire study (hospital phase, weeks 0-6; home intervention phase, weeks 7-14). WC participants will wear the Fitbit Flex, and daily steps will be measured until they complete all 3 phases that are assigned to their group: hospital phase, weeks 0-6; home wait period, weeks 7-14; and home intervention, weeks 15-22. The Fitbit Flex has evidence to support good-to-excellent validity and reliability for measuring step counts across a variety of populations, both general [53] and clinical [54], and moderate data to support validity for pediatric patients with cancer [55]. Additional rationales for the Fitbit Flex include ease of use, robust memory (30 days), water resistance, the small size of the monitor unit, and low cost. Although Actigraph GT3x monitors have more evidence to support their use among pediatric patients with cancer and are considered the gold standard [55], we chose not to use them due to their short storage capacity (42 days max) and an inability for both the participant and the telecoach to view and monitor their steps (app and web-based feedback; a critical component of coaching). Step counts are inversely associated with mortality [56], as well as fatigue and cumulative symptoms among patients with pediatric cancer [57].

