### Strengths and Limitations

Considering that this program can be remotely delivered, it has the potential to be carried forward in a scale-up RCT. This is important, considering that the average sample size for an RCT for pediatric patients with cancer has been found to be 24 people (7 studies, mean sample size=24, SD 9) [29]. This indicates a need for large, multisite trials. Another strength of this study is that the chosen games incorporate child-appropriate themes and music. Music-based interventions can improve mental health among pediatric patients with cancer, as demonstrated by improvements in anxiety, pain, depression, state of mind, self-esteem, and quality of life [63].

This is a preliminary pilot study with a high focus on participant engagement and a small sample size. Should this trial be successful in improving physical activity levels and health, future research efforts will be needed to confirm the study findings in larger sample sizes using objective biomarkers of health.

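### Steps per day is the primary outcome, but it is tested between arms at five time points at the 5% level and none of them is named as the primary contrast.

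*Protocol article*

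**What the plan says.** The section on Aim 1, which its heading labels the primary outcome, defines the measure: "Physical activity level will be measured by steps per day using a Fitbit Flex 2 wrist-worn tri-axial accelerometer". It gives the wear periods for each group but not the time point or phase on which the primary result is judged.

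The Measures section states that "There are a total of 5 data collection time points that will be compared between groups": week 0, about week 3, about week 6, week 10 and week 14. The Statistical Analysis section applies these to both outcome aims ("For aim 1 and aim 2 (measures of outcomes), outcomes will be modeled using all available measures") and sets the comparison: "Changes in means will be estimated with confidence intervals and compared between groups at 5 time points, which are baseline (week 0), posttransplant", then the three later time points. The testing rule is general: "Statistical tests will be 2-sided and will be performed using a significance level of" .05. Aim 3 rates are handled by estimates with 95% CIs.

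Aim 2 comprises two outcomes ("Health outcomes will include self-reported global health and lung function"), and the Introduction describes that aim as exploratory. Under Strengths and Limitations, the Discussion opens a conditional statement with "Should this trial be successful in improving physical activity levels and health" and goes on to call for confirmation in larger samples.

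**The concern.** Naming the measure does not fix the primary result when that measure is compared at several times under the same rule. As written, a significant difference in steps at about week 3, about week 6, week 10 or week 14 would equally meet the stated test. The choice among them could be made after the results are known.

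The rest of the article does not settle it. The Abstract describes the effect of a 14-week program, while the first aim in the Introduction describes an 8-week one. A reader cannot infer from the period of interest which visit counts.

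The week 0 entry has a separate problem. Either it is a change from baseline, which is zero by construction, or it is a difference in levels before treatment, which under randomization is chance. Neither estimates a program effect.

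The trial is meant to inform a larger one. If the most favorable of several visits is carried forward as the primary finding, the signal for that trial will tend to be too optimistic.

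**Working it through.** **Inputs from the protocol article**
- Significance level: 0.05, two-sided, for each test (Statistical Analysis).
- Time points compared between arms: 5, of which 4 are after baseline (Measures; Statistical Analysis).
- Primary outcome: steps per day, with no primary time point (Aim 1).
- Patients: 16, 8 per arm (Study Design and Overview; Randomization).

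**Assumed:** the correlation between the contrasts at different visits. The document gives none, so a range from 0 to 0.8 is shown.

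The plan states no overall error rate for steps, so there is no figure of its own to reproduce.

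**Step 1. One prespecified contrast.** The chance of a false positive is 0.05 in either direction and 0.05 / 2 = 0.025 in the program's favor.

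**Step 2. Four post-baseline contrasts, independent.**
- Either direction: 1 − (1 − 0.05)^4 = 1 − 0.8145 = 0.185.
- Favorable direction: 1 − (1 − 0.025)^4 = 1 − 0.9037 = 0.096.

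**Step 3. Four post-baseline contrasts, correlated.** Four equally correlated standard normal statistics were simulated under no effect. The table counts |z| > 1.96 at any visit (either direction) and z > 1.96 at any visit (favorable).

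| Correlation | Either direction | Favorable |
|---|---|---|
| 0 | 18.5% | 9.6% |
| 0.5 | 15.5% | 7.8% |
| 0.8 | 11.4% | 5.7% |

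**Step 4. Check at the trial's own size.** Trials with 8 per arm were simulated under no effect (20,000 per setting), with t-tests on change from baseline at the four later visits and a correlation between visits of 0.3, 0.5 or 0.7. At least one P<.05 occurred in 15.7%, 16.0% and 16.2% of trials, and in the favorable direction in about 8%.

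These results barely move, for a simple reason. With equal variances and a common correlation r between visits, each change has variance 2(1 − r) and any two changes have covariance 1 − r. Their correlation is therefore 0.5 whatever r is, which is the middle row above. In the same simulations a single contrast, the last one, gave 5.0-5.4%.

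**Step 5. Week 0.** Change from baseline at week 0 is (week 0 value) − (week 0 value) = 0 for every patient. It is left out of the counts above, because no result there could be read as a program effect.

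**The case against.** The strongest reply is that this is a condensed article about a pilot. A multiplicity rule or a primary time point may stand in a full protocol or analysis plan that is not shown, and its absence here would not be an error. Comparing arms at several visits with estimated marginal means and CIs is an ordinary longitudinal summary. The effects are called preliminary, no passage makes P<.05 the criterion for going on, and the success sentence itself asks for confirmation in larger samples.

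Much of this stands, and it limits the point in four ways.
- A reader might infer that every outcome is tested. The document does not support that: Aim 3 is only estimated.
- A reader might pool all outcomes and visits into one much larger error rate. That would ignore the stated order of a primary outcome and exploratory health outcomes. It would also need assumed correlations between outcomes, and would have to settle whether the two extra survey items are tested at all ("The last 2 questions are not scored as part of global health; instead, they are reported as raw response scores").
- A reader might add that the trial is underpowered. The article claims no power, so there is nothing to contradict.
- Only a favorable post-baseline result could be taken as success, so the favorable-direction figure is the more relevant one.

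What does not stand is that the point is merely missing detail. The article positively sets a 5% test at each of several visits for its primary outcome, lists week 0 among them, and words success as efficacy. The inflation follows from the rule as written.

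**Conclusion.** The point holds for steps per day. Under the stated rule, the chance of at least one false-positive post-baseline result is about 11-19%, with about 16% under a plain repeated-measures structure, against 5% for one named contrast. In the program's favor it is about 6-10%, against 2.5%. That is roughly two to four times the rate for a single test on either count.

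The figures assume no true effect, equal correlation of 0 to 0.8 between contrasts, and simple z- or t-tests standing in for the planned mixed-model contrasts. A different correlation within that range does not change the conclusion.

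The consequence is moderate. The call for confirmation in larger samples softens it, and the document does not say that a single significant visit would be declared a success. It leaves room for that reading and does nothing to exclude it. The change is worth making before outcome data are compared by arm.

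**What to change.** 1. Name one primary contrast: the difference between immediate start and waitlist control in change from baseline in mean daily steps at week 14, with its 95% CI. Week 14 ends the controlled comparison, before the waitlist group starts the program. It also closes both the 14-week program and its 8-week home part, so it fits either description of the aim.
2. Report the other post-baseline time points for steps, and the Aim 2 outcomes, as estimates with CIs and without significance claims. This matches what is already planned for Aim 3.
3. Remove week 0 from the between-group tests. Baseline values can be described by arm.
4. Reword the success statement so that it rests on the feasibility rates and the interval for the primary contrast.

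No new data, visits or patients are needed. The cost is fewer P values, and an effect confined to the hospital phase or early at home would be reported only descriptively. Keeping all four contrasts with a Bonferroni correction is possible, but each would then be tested at 0.05 / 4 = 0.0125, a demanding threshold with 8 per arm.

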### Ethical Considerations

Before the enrollment of participants, this study was approved by the institutional review board of the University of Alabama at Birmingham. Written informed consent and assent documentation will be obtained from all participants before their engagement in the study. Participants will receive an electronic debit card that will be loaded for US $50 for each of the data collections completed. The IS group has 5 data collections, totaling US $250. The waitlist group has 7 data collections, totaling US $350. The rationale for this value is to account for the commitment and time required of both the child and caregiver to complete the study.

The protocol and informed consent and assent forms were approved by the Institutional Review Board for Human Use of the University of Alabama at Birmingham (IRB-300012601) on June 27, 2024. Prospective participants will provide written informed consent (signed by caregivers or patients aged 18 years or older) or assent documentation (signed by children under the age of 18 years) before joining the study. Consent and assent forms will be completed in-person during the baseline data collection visit.

## Results

The study was funded in February 2024. This study started on June 27, 2024. Recruitment procedures started on June 27, 2024. This protocol paper was submitted for review before the enrollment of the first study participant. All data are anticipated to be collected by February 2026. Full trial results are anticipated to be analyzed and submitted for publication by March 2026. The study’s anticipated end date is March 31, 2026.

## Discussion

### Overview

This study will investigate the preliminary efficacy of a clinic-to-community ER program for improving both physical and mental health among pediatric patients undergoing cancer rehabilitation. The program incorporates off-the-shelf supplies, and most study procedures are done through telecommunications, which are 2 elements that will enhance the likelihood of scaling up the program into a multisite clinical trial. A program that can remotely link patients with pediatric cancer with ER health specialists through the internet could benefit this population. Incidence rates of cancer among pediatric patients and young adults are far lower than incidence rates among middle-aged and older adults [62]. Moreover, pediatric patients with cancer have limited options to improve their physical activity and mental health levels, particularly during their stay in the hospital [29].

### Strengths and Limitations

Considering that this program can be remotely delivered, it has the potential to be carried forward in a scale-up RCT. This is important, considering that the average sample size for an RCT for pediatric patients with cancer has been found to be 24 people (7 studies, mean sample size=24, SD 9) [29]. This indicates a need for large, multisite trials. Another strength of this study is that the chosen games incorporate child-appropriate themes and music. Music-based interventions can improve mental health among pediatric patients with cancer, as demonstrated by improvements in anxiety, pain, depression, state of mind, self-esteem, and quality of life [63].

This is a preliminary pilot study with a high focus on participant engagement and a small sample size. Should this trial be successful in improving physical activity levels and health, future research efforts will be needed to confirm the study findings in larger sample sizes using objective biomarkers of health.

### Conclusions

Should the findings of this study suggest that the program can improve physical activity levels, global health, and lung function, the study may discover an innovative and scalable method of intervention among pediatric patients with cancer undergoing rehabilitation.

## Appendix

Multimedia Appendix 1 Peer-review report by Kaul Pediatric Research Institute - KPRI Grant Program - The University of Alabama at Birmingham (USA).

## Abbreviations

BMT: bone marrow transplant
ER: extended reality
IS: immediate start
NIH: National Institutes of Health
PGH-7+2: NIH PROMIS Pediatric Global Health scale Short Form 7+2
PROMIS: Patient-Reported Outcomes Measurement Information System
RCT: randomized controlled trial
REDCap: Research Electronic Data Capture
WC: waitlist control
